## Expected benefits

In the military context, physical activities are associated with a high rate of fall-related injuries. Consequently, a key challenge for military medics is to identify individuals who are at-risk, in order to be able to offer them personalized preventive countermeasures to reduce their risk. There is a need to develop a tool that can assess risk factors that are amenable to a prevention strategy that reduces the risk of injury. One of the outcomes of the POSITION project will be the development of a tool to identify individuals at-risk of fall injury, based on a postural balance analysis (assessed using the BESS and posturography).

In addition, the investigation of the cognitive mechanisms involved in postural awareness will provide a better understanding of inter-individual variability regarding fall injury risk during physical activities in the military context. Finally, an assessment of the ability of POTs to reduce the risk of injury will support the evaluation of the program, which is already used by the French armed forces, in preventing fall-related trauma.

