## Secondary endpoints

Criteria for meeting the study’s four secondary objectives are as follows:

- - 1. The first secondary objective comprises two evaluation criteria: 1) self-reported scores on the Postural Awareness Scale (APPENDIX 3) pre- and post-intervention, and at the start of each session; 2) variation in measures of postural balance pre- and post-intervention.
    2. The second objective also comprises two criteria: 1) self-reported scores on Cohen’s Perceived Stress questionnaire (APPENDIX 3) pre- and post-intervention, and at the start of each session; 2) variation in measures of allostatic load in saliva pre- and post-intervention (the corticotropic axis: cortisol, DHEA, oxidative stress; the autonomic nervous system: alpha amylase and chromogranin A).
    3. The evaluation criterion for the third secondary objective will be the correct prediction of the risk of fall injury by the machine learning model.
    4. The evaluation criterion for the fourth secondary objective will be the rate of fall injuries in each of the two groups (POTs *vs.* active control), in the period between the end of the study and the end of the selection course. Information about when each participant left the course will be collected from the physician responsible.

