# STATISTICAL ASPECTS

## Calculating the number of subjects required

To date, there are no data in the literature on the effectiveness of POTs in preventing sports-related injuries. However, discussions with military unit managers and medical officers suggest that a reduction in the injury rate of around 15% would be clinically relevant. Preliminary epidemiological data from the various units indicates that the rate of fall injuries is around 50%.

To determine the sample size required to observe a significant difference in rates between the two groups, we used the following parameters:

- statistical test: two-tailed
- fall rate in the active control group: 50%
- fall rate in the POTs group: 35%
- statistical significance = 0.05
- power = 0.80

Taking into account potential drop-outs (estimated at 10%), the sample should consist of 200 participants per group, for a total of 400 participants over the two years of the study.

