**Analysis of secondary objectives**

For the first secondary objective, the effect of the POTs intervention on postural awareness will be evaluated by comparing the following for the POTs group: (*i*) scores on the Postural Awareness Scale at the six measurement times (repeated measures ANOVA), and (*ii*) posturography measurements pre- and post-intervention (paired samples comparison of means).

For the second secondary objective, the effect of the POTs intervention on the psychobiological stress response will be evaluated by comparing the following measures for the POTs group at all six measurement times: (*i*) scores on Cohen’s Perceived Stress Questionnaire (repeated measures ANOVA), and (*ii*) biological stress variables (paired samples comparison of means).

For the third secondary objective, machine learning will be used to evaluate the accuracy of the predictive model of the risk of fall injury using the following calculation:

|  | $\text{Accuracy=}\frac{\text{True }\text{Fall-related injury }\text{participants + True }\text{Non-fall }\text{participants}}{\text{Total number of participants}}$ |  |
| --- | --- | --- |

where N_prediction of trauma_ is the number of participants for whom the machine learning model predicts the occurrence of a fall injury and who do, in fact, suffer a fall injury during the selection course; N_prediction of_ _good health_ is the number of participants for whom the model predicts the non-occurrence of a fall injury and who do not, in fact, suffer a fall injury during the selection course; and N_total_ is the total number of participants included in the study.

For the fourth secondary objective, the long-term effectiveness of the POTs intervention in preventing fall injuries between the end of the study and the end of the selection course will be evaluated using a comparative survival analysis (the Cox model). Survival curves for POTs and active control groups will be compared using the log-rank test.

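### The injury-prediction model is judged only by raw accuracy over all included participants, with no reference value and a denominator that does not match the numerator (minor)

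*Protocol*

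**What the plan says.** The third secondary objective is a machine-learning model that predicts fall injury from the BESS and posturography taken before the physical activities begin. Under Secondary endpoints, its criterion is "the correct prediction of the risk of fall injury by the machine learning model".

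Under Analysis of secondary objectives, "machine learning will be used to evaluate the accuracy of the predictive model of the risk of fall injury using the following calculation". The formula adds the correctly predicted injured to the correctly predicted uninjured and divides by a total. The legend says that this total "is the total number of participants included in the study". Injury is scored according to whether participants "suffer a fall injury during the selection course".

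No other performance measure, target or comparison value is given. Under Expected benefits, one outcome of the project is the "development of a tool to identify individuals at-risk of fall injury, based on a postural balance analysis".

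Four other sections bear on the denominator:

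- The sample-size section allows for 10% drop-outs.
- The End-of-study visit section ends follow-up the day after the last session, or on the day a participant leaves the course if that is earlier, whatever the cause.
- The section on early termination by the participant says that withdrawals are not replaced.
- The Statistical methods section has one rule for missing data: replacement by the group mean.

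**The concern.** Two features of the stated formula make its result hard to read.

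First, accuracy moves with the injury rate. A model that ignores every measurement and always gives the more common answer already earns a score set by prevalence alone. Without that score beside it, a reported accuracy cannot be interpreted. The difficulty grows here because the two groups are expected to have different injury rates, so the uninformative score differs by group.

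Second, a prediction can be counted as correct only if the participant's injury status is observed, yet the denominator holds everyone included. The text does not say how someone without an observed status enters the formula. The missing-data rule does not help: the mean of a yes/no variable would be 0.50 or 0.35 at the planning rates, which is not a status.

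The window is also loose. The formula scores injuries during the selection course, whereas study follow-up ends after the last session, and the fourth secondary objective treats the rest of the course as a separate period.

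At stake is the meaning of the figure reported for a tool that the protocol presents as a product of the study.

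**Working it through.** **Inputs (Protocol, Calculating the number of subjects required)**

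- "fall rate in the active control group: 50" and "fall rate in the POTs group: 35", both in per cent.
- Two-sided 5% level, power 0.80, 10% drop-outs, 200 per group, 400 in total.

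**The plan's own figure.** No number is stated for the third objective. The sample size to which these inputs belong does reproduce closely. The two-proportion formula with continuity correction gives 183 per group. Then 183 / 0.90 rounds up to 204, or 183 × 1.10 rounds up to 202, against the stated 200.

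**Step 1: accuracy of a model with no information.** The rule that always predicts no injury has accuracy 1 − injury rate.

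- Active control: 1 − 0.50 = 50%.
- POTs: 1 − 0.35 = 65%.
- Equal groups pooled: rate (0.50 + 0.35) / 2 = 0.425, so accuracy is 57.5%.
- This rule has sensitivity 0%, specificity 100% and balanced accuracy (0 + 100) / 2 = 50%.
- The background section cites lower-limb trauma of 30–45% in selection courses. If fall injury had those rates, the same rule would score 70% to 55%.

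**Step 2: effect of the denominator.** Assume that all 10% drop-outs (40 of 400) lack an observed outcome, are split equally between groups, and do not differ in risk. The protocol does not state any of this. Then 360 have a known outcome: 180 × 0.50 + 180 × 0.35 = 90 + 63 = 153 injured, and 207 not injured.

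| Model | Known outcomes only | 40 kept in denominator only | 40 counted as uninjured |
| --- | --- | --- | --- |
| Always no injury | 207/360 = 57.5% | 207/400 = 51.75% | (207 + 40)/400 = 61.75% |
| Truly 75% accurate | 270/360 = 75% | 270/400 = 67.5% | depends on predictions for the 40 |
| Perfect | 360/360 = 100% | 360/400 = 90% | depends on predictions for the 40 |

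**Step 3: sensitivity to the assumed share d without an outcome.** With these participants in the denominator only, reported accuracy = (1 − d) × accuracy among known outcomes. If they count as uninjured, the constant rule scores 0.575 × (1 − d) + d.

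| d | Ceiling | Truly 75% reads | Constant rule, denominator only | Constant rule, counted uninjured |
| --- | --- | --- | --- | --- |
| 5% | 95% | 71.3% | 54.6% | 59.6% |
| 10% | 90% | 67.5% | 51.75% | 61.75% |
| 20% | 80% | 60.0% | 46.0% | 66.0% |

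The direction of the distortion depends on a handling choice that the formula leaves open.

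**The case against.** The strongest reply is that the classes are nearly balanced at the planning rates, so this is not the rare-event setting in which accuracy misleads badly. The uninformative score of 57.5% lies well below the 75% that the protocol reports for its preliminary posturography work. That stands, and it limits the size of the point. But the 75% is background and not a reference value for this objective.

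A statistical analysis plan, not shown here, may add measures and a validation scheme. That also stands, so their absence is not the finding. The finding is the single criterion and the denominator that the protocol does fix.

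Three stronger readings are tempting, and the document does not support them.

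- *A useless model could pass.* No pass mark exists, so nothing passes or fails.
- *The model will be scored on the data used to fit it.* A denominator of all participants is also what cross-validation gives, since each person is predicted once while held out. The protocol does not state in-sample scoring or a number of features, so no optimism can be computed from it.
- *About 40 participants will have an unknown outcome.* The 10% is a drop-out estimate. The course medic records injuries, leavers have a visit on the day they leave, and data up to withdrawal may be used unless the participant objects. In the marine commando course that prompted the project, medical unfitness accounts for 70% of failures, so many leavers may be injured with a known status. Someone who leaves uninjured is known to be injury-free up to that day, with shorter exposure.

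The planned flow chart does foresee exclusions from analysis, but the legend of the formula still counts everyone included. Leaving group out of the predictors follows from the stated objective and is not an error.

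**Conclusion.** The concern holds as a minor point. Raw accuracy is the only criterion stated, it depends on prevalence, and no reference value accompanies it. At the planning rates a model without information scores 57.5% overall, 50% in controls and 65% in the POTs group, so a reported figure near 60% would say little or nothing.

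The denominator does not match the numerator. The size of that effect rests on the assumption that drop-outs equal missing outcomes: at 10%, the ceiling is 90% and a true 75% reads 67.5%, or the constant rule reads 61.75% if these participants count as uninjured. The real share is not given and is probably smaller, because most leavers are better described as censored than as unknown.

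Only a secondary objective is affected. The primary analysis and the sample size do not depend on it.

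**What to change.** Under Secondary endpoints and Analysis of secondary objectives:

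- Define the denominator as participants whose fall-injury status is observed over one stated window, either the intervention period or the whole course. State how early leavers are counted, and report how many there are.
- Make the AUC with a confidence interval, plus sensitivity and specificity, the criterion, computed on predictions for participants not used to fit the model.
- Report accuracy beside the majority-class rate, overall and by group.

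The validation scheme, censoring-weighted models and the use of group as a predictor can be left to the statistical analysis plan.

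The cost is a change of analysis wording and little extra computing, with no new data. The downside is that the reported performance may look less favourable.

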# QUALITY CONTROL AND ASSURANCE

## Quality control

A clinical research associate will be appointed by the sponsor. This person will visit each facility on a regular basis: when the study is set up, once or several times during the course of the study, depending on the rate of inclusion, and at the end of the study. The elements to be reviewed during these visits, and their frequency, will be defined before the study is set up, in collaboration with the coordinating/principal investigator and the scientific manager, and in accordance with the study’s risk assessment.

The study has been classified as an interventional study with minimal risks and constraints, falling under risk category B.

During these visits, the following elements will be reviewed:

- compliance with the research protocol, the procedures defined therein and the regulatory texts in force,
- the quality of data recorded in the Case Report Form: accuracy, missing data, consistency of data with source documents (medical records, appointment books, original laboratory results, etc.),
- the management of any products and samples that may be collected.

A written report will be drawn up following each visit.

## Audit and inspection

An audit may be carried out at any time by persons mandated by the sponsor, and independent of those in charge of the study, or during an inspection conducted by health authorities or the French Data Protection Authority (Commission Nationale Informatique et Libertés). The aim is to ensure the quality of the study, the validity of its results, and compliance with any legislation and regulations in force.

Auditors/inspectors must be given direct access to source and medical data and any other documents relevant to the conduct of the clinical study.

Data confidentiality and participant anonymity will be respected.

The persons who direct and supervise the study agree to comply with the requirements of the sponsor and the competent authority with regard to an audit or inspection.

The audit can be applied to all stages of the study, from the development of the protocol to the publication of the results, and the classification of data used or produced in the context of the study.

## Commitment to responsibility

Before the study begins, each investigator will provide an up-to-date, dated and signed curriculum vitae (CV) to the sponsor’s representative. The CV will include an RPPS number (The Directory of Health, Social work and Medico-Social Professionals in France), the number the person is registered under with the Ordre des Médecins (the French National Medical Council) (excluding military physicians), and details of any previous participation in studies and training related to clinical research.

Each investigator agrees to comply with legislative and regulatory obligations, and to conduct the study in accordance with regulations, and in compliance with the current Declaration of Helsinki. The principal investigator will sign an undertaking of responsibility, which will be given to the sponsor’s representative.

The investigators and their collaborators will sign a form that designates the allocation of tasks and specifies their role, and each person will provide a copy of their CV.

# ETHICAL AND REGULATORY CONSIDERATIONS

## Ethical justification

### The distinction between care and research

In the context of the POSITION project, both POTs and active control interventions, together with all measurements carried out, relate to research activities.

### Benefit/ risk ratio

#### Benefits

Individual benefit(s):

The POSITION project will test the effectiveness of a POTs intervention in preventing fall injuries during physical activities in the military context. In addition, the study will seek to describe the risk and protective factors that moderate the occurrence of an injury, including cognitive mechanisms involved in postural awareness, and the psychobiological stress response. The outcomes of this study are expected to support the development of new, evidence-based prevention/medical strategies that can predict the risk of fall-related injury during physical activities in the military context, together with their prevention due to a POTs intervention. The expected benefits of this study relate to the protection of the health of combatants in the context of their military service.

Group benefit(s):

On a group level, the prevention of fall injuries will improve the health of the military population, and consequently their ability to carry out their missions. Benefits relate to both the health and the safety of combatants in the context of their military service.

#### Risks

Individual risk(s)

No individual risk directly related to the POSITION protocol can be identified.

Group risk(s)

No group risk directly related to the POSITION protocol can be identified.

#### Benefit/risk ratio

The benefit/risk ratio is positive, as the study has both individual and group benefits, and there no risks can be identified that are directly related to the POSITION protocol.

### Methodological choices

In the context of the POSITION project, all measurements are related to the research being carried out; therefore, no additional monitoring modalities are planned.

## Compliance with regulations and legislation

The study will be conducted in accordance with the present protocol, and in compliance with the Declaration of Helsinki (as modified in Fortaleza in 2013 Cf. full version), Good Clinical Practice recommendations (GCP, ICHE6) and any locally applicable regulations.

As this study falls within the definition given in 2° of Article L.1121-1 of the French Public Health Code, it requires approval from an Institutional Review Board.

In accordance with the conditions set out in Article L 1121-10 of the French Public Health Code, the French State assumes responsibility for compensating those involved for any harmful consequences of the study.

In the event of a favorable decision, the sponsor will forward the opinion of the Institutional Review Board and the summary of the protocol to the French Medicines Agency (Agence nationale de sécurité du médicament et des produits de santé) for information.

The data recorded during this study will be digitally processed at IRBA in compliance with Law No. 78-17 of January 6, 1978 relating to information technology, files and freedoms as amended by Law 2018-493 of June 20, 2018 and the General Data Protection Regulation (Articles 6.1.f, 9. *j* and Article 13).

This study falls within the scope of the ‘Reference Methodology’ (MR-001) following the application of the provisions of Article 73 of the amended law of January 6, 1978 relating to information, files and freedoms. The French Defence Health Service Headquarters (Direction centrale du service de santé des armées), the sponsor of this study, has signed a commitment to comply with this Reference Methodology.

The data controller for the French Armed Forces Medical Corps is the Central Director of the Armed Services Health Service. The Data Protection Officer (DPO) is the Director of Legal Affairs of the Ministry of the Armed Forces. The data controller’s representative, who is the contact point for the ministerial DPO, can be contacted at [contact].

## Protocol amendment

Any substantial modification, in other words, any modification that is likely to have a significant impact on the protection of individuals, the validity and outcomes of the study, the interpretation of supporting scientific documents, or the methods used, must be the subject of a written amendment submitted to the sponsor, who must obtain a favorable opinion from the Institutional Review Board prior to its implementation.

Non-substantial modifications, in other words, those that do not have a significant impact on any aspect of the study, must be communicated to the Institutional Review Board for information purposes.

All amendments to the protocol must be brought to the attention of all healthcare professionals taking part in the study, who undertake to respect them.

# CONSERVATION OF DOCUMENTATION AND DATA

The following documents relating to this study will be archived in accordance with Good Clinical Practice **for a period of 15 years** following the end of the study:

- By the investigators:
- The protocol and any amendments to the protocol,
- A copy of participants signed informed consent forms,
- Case Report Forms,
- Participants’ personal files,
- All other research-related documents and correspondence.

All these documents are the responsibility of the physician for the duration of the regulatory archive period.

- By the sponsor:
- The protocol and any amendments to the protocol,
- A copy of participants signed informed consent forms,
- Original Case Report Forms,
- All other research-related documents and correspondence.

All of these documents are the responsibility of the sponsor for the duration of the regulatory archive period.

Nothing may be moved or destroyed without the sponsor’s consent. At the end of the regulatory archive period, the sponsor will be consulted before destruction, and must give written agreement. All data, documents and reports may be subject to audit or inspection.

# PUBLICATION RULES

## Scientific communications

Data analysis will be carried out by the IRBA. This analysis will result in a written report that will be submitted to the French Defense Health Service Headquarters (Direction centrale du Service de santé des armées). This report will be used in the preparation of one or more publications.

Any written or oral communication of the outcomes of this study must receive prior approval from the person who directs and supervises it, and, where applicable, any committee set up in the context of the project.

The report of the main results will include the name of the sponsor (Direction centrale du Service de santé des armées), all the healthcare professionals who included or monitored patients, the methodologists, biostatisticians and data managers who took part, and members of related committee(s). International reporting and publication rules will be followed (Vancouver Convention, February 2006; Recommendations for the Conduct, Reporting, Editing, and Publication of Scholarly Work in Medical Journals Updated, IJCME, 2018).

